### Statistical analysis

2.8

In this study, SPSS25.0 statistical analysis software is used for data analysis, and the measurement data are expressed by ($\bar{\text{x}}\pm \text{S}$). For the data that accord with normality and homogeneity of variance, group *t* test is used between groups, paired *t* test is used within groups, rank sum test is used for those who do not conform to normal distribution, and *χ*^2^ test is used for counting data. When *P* *<* 0.05, it is statistically significant.

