### Sample size calculation

2.4

This study was a pilot clinical trial. According to the analysis and calculation of the related literature published in the past 10 years, the therapeutic efficiency of Western medicine is 72.3%, and the effective rate of traditional Chinese medicine combined with Western medicine is 92.1%. Using the sample size estimation formula compared with multiple sample rates, set the significance test level α = 0.05, then μ_α_ = 1.96, 1−β = 0.9, μ_β_ = 1.28. δ = π_1_−π_2_ sample size estimation formula for comparison of 2 sample rates:$$N_{1}=N_{2}={\left(\frac{\mu_{\alpha }+\mu_{\beta }}{\delta }\right)}^{2}[\pi_{1}(1-\pi_{1})+\pi_{2}(1-\pi_{2})]$$

The sample size of each group is calculated to be 73. Considering shedding and other factors, the expansion is about 20%, and it is calculated that 182 patients need to be included. According to the simple randomized method, the patients included in the study are divided into control group (n = 91) and the observation group (n = 91).

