### Data collection and management

2.7

The data are collected according to the evaluation criteria before the beginning of treatment, 72 hours after the treatment and at the end of treatment. Thirty days after the end of treatment, each patient is followed up by outpatient or telephone. The reasons for the loss of follow-up cannot be collected. All data will be collected jointly by 1 or 2 assistants. Personal information about potential participants and registered participants will be collected, shared, and stored in a separate storeroom to protect before, during, and after confidentiality. The access to the database is limited to the researchers of this research group.

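### Section 2.8 lets the trial data choose between t and rank-sum tests, leaves one case without a test, and can test an outcome on means at one visit and on ranks at the next

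*Protocol article*

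**What the plan says.** Section 2.8 (Statistical analysis) summarises measurement data as mean and SD and then sets the tests. The two-group t test is used "For the data that accord with normality and homogeneity of variance". The alternative is narrower: "rank sum test is used for those who do not conform to normal distribution". No outcome is assigned to either test beforehand.

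Section 2.6 lists seven continuous outcomes. Four are main outcomes (TCM syndrome score, NT-proBNP, LVEF, BNP) and three are secondary (SV, LVESD, LVEDD). Section 2.7 collects data "before the beginning of treatment, 72 hours after the treatment and at the end of treatment", so each outcome has two assessments after baseline. Section 2.4 plans 73 per group before losses and 91 per group after, allocated 1:1.

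**The concern.** Three things follow from the wording.

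1. The t test needs two conditions, but the fallback covers failure of only one. Normal data with unequal variances fall between them, and the analyst would have to pick a test after seeing the data.
2. The choice depends on the observed data, and nothing ties the two assessments of one outcome together. The 72-hour result could be a test of means and the end-of-treatment result a test of ranks. These answer different questions.
3. The rank-sum test responds to differences in spread and shape as well as in location. A significant rank-sum result printed beside two means and SDs invites the reader to conclude that the means differ, which that test does not establish.

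At stake is which quantity the trial tests for each outcome and, in some circumstances, the 5% level for the mean difference that readers will see.

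**Working it through.** **The plan's own figure.** Section 2.4: "set the significance test level α = 0.05" (1.96), power 0.9 (1.28), rates 72.3% and 92.1%.

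((1.96 + 1.28)/0.198)² × [0.723×0.277 + 0.921×0.079] = 267.77 × 0.27303 = 73.11 per group, which agrees with "The sample size of each group is calculated to be 73". Then 2 × 73/(1 − 0.2) = 182.5, against the stated 182. The present point does not affect the sample size; it only supplies the range of 73 to 91 per arm used below.

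**Assumptions.** The article names no diagnostic, cut-off, SD or distribution. The simulations assume Shapiro-Wilk in each arm and Levene's test, both at 5%, with equal true means.

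**The undefined case** (normality passes, equal variance fails). With 80 per arm and normal data it arises in about 5% of comparisons at equal SDs, 29% at SD ratio 1.2 and 54% at 1.3. With 73 and 91 per arm and SD ratio 1.5 it arises in 81% and 85%.

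Its numerical effect is small. With equal arms the Student and Welch statistics are identical and only the degrees of freedom differ. At 80 per arm and SD ratio 1.3, Welch has 79 × (1 + 1.69)²/(1 + 2.8561) = 148, against 158 for Student. For SD ratios of 1.0–1.5 the two tests disagreed on significance in at most 0.02% of trials, and both rejected in 4.8–5.4%. If the case is sent to rank-sum instead, SD ratio 1.5 gives 5.7% (73 per arm) and 5.1% (91 per arm).

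**Different tests at two visits** (assumed between-visit correlation 0.7).

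- 73 per arm, counting any change among t, rank-sum and undefined: 24% for normal data, 39% for mild log-normal skew (log-SD 0.1–0.2), 12% for log-SD 0.3.
- 80 per arm, gamma data with skewness 0.5: 42%.

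The rate falls again with stronger skew because rank-sum is then chosen at both visits.

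**Rejection rate with equal true means**, 80 per arm, undefined case filled with Welch:

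| SD ratio | Skewness, two arms | Rule | Welch |
|---|---|---|---|
| 1.0 | 0.5 / 0.5 | 5.9% | 5.6% |
| 1.3 | 0.5 / 0.5 | 5.2% | 4.5% |
| 1.5 | 0.7 / 0.7 | 7.8% | 4.8% |
| 1.3 | 0.5 / 1.0 | 8.3% | 4.5% |
| 1.3 | 1.0 / 1.5 | 9.9% | 4.8% |
| 1.5 | 1.0 / 1.0 | 10.1% | 4.2% |
| 1.5 | 0.5 / 1.0 | 11.0% | 5.6% |

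Runs were 3,000 per row (4,000 in the second). The simulation standard error near 5% is √(0.05×0.95/3000) = 0.4 percentage points.

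A second set used 73 / 91 per arm, 6,000 runs, and rank-sum in the undefined case:

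| Distribution | Rule | Welch |
|---|---|---|
| Identical in both arms | 4.6–5.5% / 5.0–5.2% | 4.4–5.0% / 4.7–5.2% |
| Normal, SD ratio 2 | 6.2% / 6.1% | 4.9% / 5.1% |
| Gamma, shape 4 v 8 | 9.4% / 10.7% | 5.0% / 5.4% |
| Log-normal, log-SD 1.0 v 0.8 | 21.3% / 24.9% | 5.3% / 5.0% |

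The excess needs skewness together with a difference in spread or shape. It appears whichever way the undefined case is filled.

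**The case against.** The strongest reply is that this is a condensed article. The diagnostic, its cut-off and the unequal-variance fallback are details commonly left to the full protocol or SAP. That stands for the diagnostic and the cut-off, whose absence is not criticised here. It does not dispose of the rule itself, which the article states and which makes the test depend on the trial data under any diagnostic.

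A reader might infer that the stated 5% level simply fails. The documents do not support that. The arms are randomised, so if treatment does nothing they share one distribution and the rule holds about 5%. The excess arises only if treatment alters spread or shape, leaves the means exactly equal, and the data are skewed. Treatment has then changed something, and the rank-sum test is detecting a real difference, though not one in means. A treatment to which only some patients respond would usually move the mean as well.

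A reader might also infer that the undefined case distorts results. With 1:1 arms it barely does, because the two t tests nearly coincide. Nor is it sound to argue that 7 outcomes × 2 visits give 1 − 0.95¹⁴ = 51% chance of meeting it at least once. That needs 14 independent, normal comparisons, and these outcomes are related (NT-proBNP with BNP, and the echocardiographic measures with each other). Skewed outcomes hardly ever reach it: about 0.05% per comparison at skewness 1 with equal SDs.

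Finally, applying the choice separately at each visit is a reading of the text. Section 2.8 does not require it, but neither does it prevent it.

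**Conclusion.** The point holds in a conditional form. Two parts follow from the wording alone: normal data with unequal variances have no named test, and one outcome may be tested on means at one visit and on ranks at the other while being displayed as mean and SD.

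The error-rate part depends on assumptions. At 80 per arm and SD ratios of 1.3–1.5 the rule rejects in about 6–11% of trials with equal true means, against about 5% for Welch. The excess almost disappears at the mild end (5.2% at SD ratio 1.3 and skewness 0.5 in both arms). It would be larger for strongly skewed outcomes, but the article gives no distributions from which to judge that. The main harm is the switch to ranks, not the missing branch. The change is worth making because the fixed alternative is better and nearly free.

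**What to change.** Replace the rule in section 2.8 with one between-arm test per outcome, fixed in advance and the same at 72 hours and at the end of treatment, covering all seven continuous outcomes:

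- **TCM syndrome score, LVEF, SV, LVESD, LVEDD:** Welch's unequal-variance t test whatever the normality or variance checks show, reported as a mean difference with 95% CI.
- **NT-proBNP and BNP:** one pre-named analysis, for example Welch's t on log-transformed values, reported as a ratio of geometric means with 95% CI. This targets geometric rather than arithmetic means, so the summary table should match.
- **Rank-sum:** only as a named sensitivity analysis.

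The two natriuretic peptides must be included. They are two of the four main outcomes, and dropping the rule without assigning them a test would leave a wider gap than the present one.

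The cost is a few lines of text. If variances are in fact equal, the power lost by using Welch's test at 73 to 91 per arm is negligible.

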### Patients

2.3

Inclusion criteria: meet the diagnostic criteria of coronary heart disease, refer to the 2017 Chinese guidelines for Prevention and treatment of Cardiovascular Diseases; meet the diagnostic criteria of chronic heart failure,^[13]^ Doppler ultrasound indicates that the left ventricular ejection fraction is less than 50%,^[14]^ and the condition was in stable stage; age 40 to 79 years old; all patients signed consent.

Exclusion criteria: patients with other serious cardiovascular diseases; patients with other serious diseases such as malignant tumors; patients with severe mental illness; patients who are allergic to or have contraindications to medication in this study; unable to understand the study plan or unwilling to participate after explanation.

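### The between-arm tests make no baseline adjustment, and within-arm paired tests share the same P < 0.05 rule with no statement that only the between-arm contrast decides efficacy

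*Protocol article*

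**What the plan says.** Section 2.8 (Statistical analysis) names four procedures. Normally distributed measurements with equal variances are compared between arms by a group t test. A paired t "test is used within groups, rank sum test is used for those who do not conform to normal distribution". Counts go to a chi-square test. Measurement data are summarised as mean and SD, and one threshold, P < 0.05, covers every test.

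Section 2.7 (Data collection and management) sets the timing: "The data are collected according to the evaluation criteria before the beginning of treatment", then again at 72 hours and at the end of treatment. The main outcomes in section 2.6 (TCM syndrome score, NT-proBNP, LVEF, BNP) and the secondary ones (stroke volume and two ventricular diameters) therefore have baseline values.

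Section 2.5 gives nitroprusside and the same routine drug treatment to both arms; only Shenfu differs. Section 2.4 uses simple randomisation.

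Section 2.8 does not say whether the between-arm test uses end values or changes, names no covariate, and does not say which test decides efficacy.

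**The concern.** There are two separate issues.

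**Efficiency.** When an outcome is measured before treatment, regressing the end value on arm and baseline gives a more precise treatment estimate than a t test on end values or on changes, provided baseline and end value are correlated. It also corrects for chance baseline imbalance, which simple randomisation leaves possible. In addition, the switch between t test and rank-sum test depends on how the data look, and no effect estimate is named for either route.

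**Interpretation.** The paired tests are planned as inferential tests at the same threshold as the between-arm tests. Because both arms are actively treated, patients may improve in both with no contribution from Shenfu. A small P value inside the Shenfu arm, or one there and not in the control arm, is not evidence for Shenfu. The closing part of the Discussion states the aim as verifying improvement in symptoms and cardiac function, which a reader could wrongly take a within-arm P value to satisfy.

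**Working it through.** **1. The plan's own figure.** Section 2.4 has "set the significance test level α = 0.05", a critical value of 1.96 (hence two-sided), 1.28 for 90% power, and effective rates of 72.3% and 92.1%. Its formula gives

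((1.96 + 1.28)/0.198)² × [0.723 × 0.277 + 0.921 × 0.079] = 267.77 × 0.27303 = 73.1,

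which agrees with "The sample size of each group is calculated to be 73". Dividing by 0.8 for dropout gives 91.25, stated as 91 per arm and 182 in total. This sample size rests on a binary rate, so the present point does not alter it. It supplies the n of 73 used below.

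**2. Variance.** Let r be the correlation between baseline and end value, with equal SDs at both times. In units of the end-value variance:
- end-value t test: 1
- change-score t test: 2(1 − r)
- ANCOVA: 1 − r²

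The ratio of ANCOVA to the end-value test is 1 − r²: 0.75 at r = 0.5 and 0.51 at r = 0.7. The ratio of ANCOVA to the change score is (1 − r²)/(2(1 − r)) = (1 + r)/2: 0.75 and 0.85. Neither ratio exceeds 1, so ANCOVA is at least as efficient on either reading of section 2.8.

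**3. Power.** Two-sided t-test power at 73 per arm and 0.05, with the standardised effect d divided by the square root of the variance above. Both d and r are assumed.

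| d | r | End value | Change score | ANCOVA |
|---|---|---|---|---|
| 0.20 | 0.5 | 23% | 23% | 28% |
| 0.20 | 0.7 | 23% | 34% | 39% |
| 0.35 | 0.3 | 56% | 43% | 60% |
| 0.35 | 0.5 | 56% | 56% | 68% |
| 0.35 | 0.7 | 56% | 77% | 84% |
| 0.35 | 0.8 | 56% | 91% | 94% |
| 0.50 | 0.5 | 85% | 85% | 93% |
| 0.50 | 0.7 | 85% | 97% | 99% |

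At d = 0.35 and r = 0.7 the gain is 28 points over end values (84 − 56) but only about 6 over change scores (83.7 − 77.4). At r = 0.5 it is 12 points on either reading.

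**4. Within-arm tests when Shenfu does nothing.** A simulation used 73 per arm, 20,000 trials per setting, the same true change in both arms (0.2, 0.3 or 0.5 SD), r of 0.5 or 0.7, and an SD of change of √(2(1 − r)).
- The paired test in the Shenfu arm is significant in 39% of trials (0.2 SD, r = 0.5) to nearly 100% (0.5 SD, r = 0.7).
- Significance in the Shenfu arm but not in the control arm occurs in up to 24% of trials (0.2 SD, r = 0.7). It becomes rare once the common change is large, because both arms are then significant.
- The between-arm t test is significant in about 5%, as it should be.

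**The case against.** The strongest reply is that nothing here is invalid. A between-arm test is planned and named first, it controls type I error under randomisation, and the article calls the trial a pilot. Covariates, transformations and confidence intervals are commonly left to a fuller plan. No sentence says that a within-arm P value will support an efficacy claim.

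Much of this stands. A reader might infer that the plan makes no between-arm comparison, or intends to claim efficacy without one. The text does not support that: the gap is that the two kinds of test are not ranked. A reader might also infer that baseline is certainly ignored. Section 2.8 is silent on end values or changes, and a change score does use baseline, so the larger power gains hold only on the end-value reading. The 0.35 SD effect and the correlations have no source in the documents.

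Two further inferences go too far. Since entry requires that "Doppler ultrasound indicates that the left ventricular ejection fraction is less than 50" per cent, one might expect LVEF to rise by regression to the mean. Section 2.3 does not say that the qualifying scan serves as the baseline, and such a rise would affect both arms alike, leaving the between-arm test unbiased. Nor is it right that the rank-sum route can give no effect size: a Hodges-Lehmann shift with an interval can accompany it. Section 2.8 just does not name one.

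What does not stand is the appeal to an unseen plan. Section 2.8 states its methods, and ANCOVA is at least as efficient as the stated test on either reading.

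**Conclusion.** The point holds as an improvement to a stated method and a clarification of what decides efficacy; it is not an error that invalidates the trial.

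On efficiency, the variance reduction from ANCOVA is 25% at r = 0.5 on either reading. At r = 0.7 it is 49% against end values and 15% against change scores. The corresponding power gain at 73 per arm and 0.35 SD runs from about 6 to 28 points. All of this depends on assumed correlations and an assumed effect. The gain over end values is small at low correlation, and the gain over change scores is small at high correlation.

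On interpretation, the conclusion needs no assumed figure: with nitroprusside and routine drugs in both arms, a within-arm P value cannot isolate Shenfu. The simulation only illustrates how often it could mislead, and only if someone reads it as evidence of efficacy. The change should be made before any data are analysed.

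**What to change.** Amend section 2.8 as follows.

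- Make the primary between-arm analysis of each continuous outcome an ANCOVA of the end-of-treatment value on arm and baseline value.
- Analyse NT-proBNP and BNP on the log scale and report geometric-mean ratios; report adjusted mean differences for the other outcomes. Give a 95% confidence interval for each.
- Keep the rank-sum test as a sensitivity analysis, so that the primary method no longer depends on a normality check.
- Report within-arm changes descriptively, without P values.
- State that efficacy conclusions rest only on the between-arm contrast.

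The 72-hour values can be analysed with the same model as supportive results.

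The cost is the wording, plus a routine check of model fit, including for the TCM syndrome score. The baseline data are already to be collected, SPSS 25.0 runs ANCOVA, and the sample size does not change.

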**Discussion::**

This study will evaluate the efficacy and safety of Shenfu injection combined with sodium nitroprusside in the treatment of chronic heart failure in patients with coronary heart disease. The results of this experiment will provide a clinical basis for Shenfu injection combined with sodium nitroprusside in the treatment of chronic heart failure in coronary heart disease.

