### Study design

2.5

In this study, through prehospital recruitment, in-hospital inpatients to screen patients who meet the criteria, patients and their families approve the study program and sign the informed consent form. The patients will be randomly assigned to the treatment group and the control group. Among them, the treatment group will receive Shenfu injection (Shenfu injection 40 mL injection + 5% GS 250 mL injection, ivgtt, QD) combined with intravenous drip of sodium nitroprusside (sodium nitroprusside 3 μ g / kg/min), while the control group will only receive intravenous drip of sodium nitroprusside. Patients in both groups will receive the same routine care and drug treatment, such as angiotensin converting enzyme inhibitor/angiotensin II receptor blocker, beta blocker, diuretic, etc. If necessary, the attending physician can adjust the program according to the patient's condition, and all interventions will be recorded in detail for final result analysis. We will set up a special drug manager, and the nurse will be responsible for preparing the medicine and preparing the solution. Therefore, the study is not blind to nurses, but to researchers, patients, and statisticians. All patients will receive an intravenous injection once a week. The health status of each patient is evaluated before and after treatment, including efficacy and safety indicators, and all patients are followed up by telephone for 30 days. Follow-up included cardiovascular events and rehospitalization.

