### Evaluation criteria and judgment of curative effect

2.6

1.Main outcome indicators: TCM syndrome score (refer to the guiding principles of Clinical Research of New drugs of traditional Chinese Medicine^[15]^), N-terminal pro-brain natriuretic peptide (NT-pro BNP), left ventricular ejection fraction, brain natriuretic peptide (BNP).2.Secondary outcome indicators: stroke volume (SV), left ventricular end-systolic diameter, left ventricular end-diastolic diameter.3.Adverse reactions: including abnormal liver function and uncomfortable symptoms (such as dizziness, nausea, etc) during treatment.

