The purpose of this randomized controlled trial is to verify that Shenfu injection can significantly improve the clinical symptoms and cardiac function in patients with chronic heart failure in patients with coronary heart disease. Since there is no standard clinical study to evaluate the efficacy of Shenfu injection combined with sodium nitroprusside in patients with heart failure of coronary heart disease, we intend to evaluate its efficacy and safety through prospective randomized controlled trials.

This study also has some limitations: due to the short planned follow-up time, we are unable to understand the impact of long-term results, so we may extend the follow-up time if necessary. And due to the influence of treatment, this study cannot achieve strict double-blindness, which may affect the results to a certain extent.

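### Adverse reactions fall only under a general chi-square rule at P < 0.05; with this sample size a risk difference with a 95% confidence interval would serve the safety aim better

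*Protocol article*

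**What the plan says.** The abstract states the aim: "This study will evaluate the efficacy and safety of Shenfu injection combined with sodium nitroprusside". The closing Discussion repeats it: "we intend to evaluate its efficacy and safety through prospective randomized controlled trials".

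Section 2.6 lists the safety outcome third, after the main and secondary outcomes: adverse reactions, "including abnormal liver function and uncomfortable symptoms (such as dizziness, nausea, etc) during treatment". Section 2.5 adds events from the 30-day follow-up: "Follow-up included cardiovascular events and rehospitalization". The article gives no expected rate for any of these.

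Section 2.8 does not mention safety. It is a general list of tests by type of data. For counts, the χ² "test is used for counting data. When" *P* < 0.05, the result is called statistically significant.

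Section 2.4 sizes the trial on effective rates of 72.3% and 92.1%: "The sample size of each group is calculated to be 73", enlarged by about 20% to 182 patients, or 91 per group. Adverse reactions do not enter the calculation.

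**The concern.** A test of no difference can reveal harm, but failing to reject does not show that harm is absent. How much a non-significant result tells us depends on how large an excess the trial could have detected. Here the size was fixed by an efficacy difference of 19.8 percentage points. A much smaller absolute excess in adverse reactions could matter and still go undetected.

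The abstract says the results will give a clinical basis for using the combination, so the safety result will be used. If the report gives only a P value for reactions, readers cannot tell a reassuring result from an uninformative one. The limitations name short follow-up and incomplete blinding, but not the limited information on safety.

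**Working it through.** **Inputs from the article.** Two-sided α = 0.05 with deviate 1.96, power 0.90 with deviate 1.28, effective rates 72.3% and 92.1% (all section 2.4); 1:1 allocation (abstract); 73 per group before dropout and 91 randomised (section 2.4).

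**Assumed input.** The adverse-reaction rate in the control group. The article gives none, so a range is shown.

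**Step 1: the plan's own figure.** N = ((1.96 + 1.28)/0.198)² × [0.723 × 0.277 + 0.921 × 0.079] = 267.77 × 0.27303 = 73.1. The article has 73. Allowing for 20% loss, 146/0.8 = 182.5; the article has 182. Both reproduce to within rounding. Only efficacy rates enter.

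**Step 2: chance of missing a doubling.** The approximate power for rates p₁ and p₂ with n per arm is

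Φ{ [ |p₂ − p₁|√n − 1.96√(2p̄(1 − p̄)) ] / √(p₁(1 − p₁) + p₂(1 − p₂)) }, with p̄ the mean of the two rates.

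- 5% vs 10%, n = 91: (0.477 − 0.730)/0.371 = −0.68, power 0.247, miss 75%.
- 10% vs 20%, n = 73: (0.854 − 0.990)/0.500 = −0.27, power 0.393, miss 61%.

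Exact enumeration over two binomial distributions, using the Pearson χ² test without continuity correction, gives:

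| Control vs Shenfu rate (assumed) | Missed, n = 91 | Missed, n = 73 |
|---|---|---|
| 2% vs 4% | 89% | 91% |
| 5% vs 10% | 76% | 79% |
| 10% vs 20% | 53% | 60% |
| 15% vs 30% | 32% | 41% |
| 20% vs 40% | 15% | 24% |

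For control rates of 5% to 10% the range is therefore 53% to 79%. The article does not say whether a continuity correction would be applied; with Yates' correction that range becomes 60% to 88%.

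**Step 3: what an interval adds.** Suppose 9 of 91 patients on Shenfu and 5 of 91 controls have a reaction (9.89% and 5.49%).

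- Test: χ² = 182 × (9 − 5)²/(14 × 168) = 2912/2352 = 1.24, P = 0.27.
- Wilson 95% limits for each arm: 5.29% to 17.74% and 2.37% to 12.23%. The difference is 4.40 points.
- Newcombe lower limit: 4.40 − √[(9.89 − 5.29)² + (12.23 − 5.49)²] = −3.8 points.
- Newcombe upper limit: 4.40 + √[(17.74 − 9.89)² + (5.49 − 2.37)²] = +12.8 points.

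The P value says only that the difference is not significant. The interval says that an excess of up to nearly 13 points remains compatible with the data.

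**Step 4: precision to expect.** If both arms have the same true rate, the simple half-width is 1.96√(2p(1 − p)/n). This is 6.3 points at 5% with n = 91 and 9.7 points at 10% with n = 73.

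**The case against.** The strongest reply is that section 2.8 is a generic list of tests and not a safety criterion. A reader might infer that the plan makes P < 0.05 its declared safety rule and will treat P > 0.05 as proof of safety. The article supports neither reading. It promises to evaluate safety, not to demonstrate equivalence or non-inferiority, so the absence of a margin contradicts nothing. Naming a test also does not stop the authors from reporting rates.

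A reader might also take a miss probability of half to four-fifths as a property of the plan. It is not: it rests on an assumed control rate of 5% to 10%. The endpoint in section 2.6 is broad, and if any-reaction rates reach 20% in controls, a doubling would be missed only 15% to 24% of the time. Single reaction types will, however, be no more common than the composite, and usually rarer.

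It is fair, too, that most trials sized for efficacy have little power for uncommon reactions, that section 2.4 calls this a pilot, that the closing Discussion describes the purpose mainly in terms of symptoms and cardiac function, and that a full analysis plan may contain estimation rules. These points limit the finding to an improvement. They do not remove it. Section 2.8 does state a test and a threshold for all count data, and for a safety aim a better method exists that uses the same data. The pilot label favours estimation over testing.

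**Conclusion.** The point holds as a cheap improvement, not as an error in the plan. Safety is a stated aim, the trial is sized on efficacy rates alone, and the one stated rule that covers adverse reactions cannot by itself tell no excess from too few patients. The size of the problem is conditional on a rate that the article does not supply: a doubling is missed about 53% to 79% of the time at control rates of 5% to 10%, about 90% at 2%, and 15% to 24% at 20%. These figures assume 91 to 73 evaluable patients per arm and an uncorrected two-sided 5% χ² test.

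**What to change.** In section 2.8, state that for adverse reactions (any, and each named type), and for cardiovascular events and rehospitalisation by day 30, the report will give the number and percentage of patients per arm and the risk difference, Shenfu minus control, with a two-sided 95% Newcombe interval. Say that the safety conclusion will be worded from the upper limit, that is, which size of excess the data exclude and which they do not, and that P > 0.05 will not be taken as evidence of safety. Add one sentence to the limitations: the sample size was set on efficacy and not on safety.

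This takes a few sentences and needs no extra patients or data. The downside is a more cautious safety statement.
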